### Measures

#### Selection of Standardized and Validated Study Measures

Selected study measures make use of the PhenX toolkit [78], Patient-Reported Outcomes Measurement Information System (PROMIS) Toolbox [79,80], and Health Resources and Services Administration (HRSA) HIV/AIDS Bureau reporting standards [81]. Measures were selected based on our preliminary work, theoretical model, and relevance to the population (Table 3). The PhenX Toolkit is a searchable online database of recommended measurement protocols for human studies [82]. Database protocols are well established, broadly validated, reliable, and low burden for study participants. Measures for this study, derived from the PhenX toolkit, include a set of demographic characteristics and social determinants of health, as well as the Medical Outcomes Study Social Support Survey.

**Table 3 table3:** PoPIT^a^ constructs, measures, and prospective data collection.

Construct	Measure	Collection
Participant characteristics [82]	PhenX: age, ethnicity and race, biological sex, sexual orientation, sexual identity, marital status, and educational attainment	Baseline^b^
Social determinants of health [83]	AAFP^c^ Social Needs Screening Tool: housing, food and transportation insecurity, utilities, employment, finances, and personal safety PhenX: internet access, access to health technology, and general social media use	Baseline and 12 months
Attitudes toward technology [84]	Social Media Usage & Attitudes Scale (MTUAS^d^)	Baseline, 6, and 12 months
Technology affordances [85]	Mobile Application Affordances Measure	3 and 6 months after app initiation
PPA^e^ engagement	Number of logins, duration (minutes), number of sessions, and engagement counts for each PPA function (articles, med tracker, resources, forum, and chat)	Concurrent with participant app use
Self-efficacy for managing chronic illness [86]	PROMIS^f^ subscales: managing emotions, social interactions, medication adherence, and general self-efficacy	Baseline, 3, 6, 9, and 12 months
Social support [87]	Medical Outcomes Study Subscales: emotional/informational support, tangible/instrumental support, and positive social interaction	Baseline, 3, 6, 9, and 12 months
Perceived HIV stigma [88]	HIV Stigma Scale subscales: personalized, disclosure, negative self-image, and public attitudes	Baseline, 3, 6, 9, and 12 months
Engagement in HIV care [89]	Pre- and postclinic visit dates and count	12 months before enrollment and 18 months after study completion
Viral suppression [89]	Preenrollment CD4 count and date Pre- and post-HIV viral load values	12 months before enrollment and 18 months after study completion

^a^PoPIT: Positive Peers Intervention Trial.

^b^Baseline data collection occurs at consent.

^c^AAFP: American Academy of Family Physicians

^d^MTUAS: Media and Technology Usage and Attitudes Scale.

^e^PPA: Positive Peers mobile app.

^f^PROMIS: Patient-Reported Outcomes Measurement Information System.

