### Enrollment, Randomization, and Data Collection Procedures

All participants are consented, enrolled, and randomized at the partner institution where they receive care, in partnership with the PoPIT staff, who are needed to set up the user’s PPA account. Specifically, following in-person consent at the partner site, all participants complete a preloaded baseline questionnaire on a study-dedicated tablet in the presence of study staff. While they are completing the questionnaire, the trial participant is randomly assigned in REDCap to either the intervention (immediate PPA start) or control (6-month delayed PPA start) arm at a 1:1 ratio. Participants randomized to the delayed-start arm receive usual clinic care before beginning the clinical intervention. Given our pilot findings indicating a stronger PPA effect on HIV viral suppression among participants in the youngest age group (ie, <24 years), we employ a block randomization strategy in which study arm assignment occurs separately for participants within the age groups 13-24 and 25-34 years.

Following randomization, site study staff assist participants randomized to the immediate-start arm in downloading the PPA from the public app store using the participant’s personal phone. Site study staff guide participants through in-app tutorials demonstrating how to use app features. Participants randomized to the delayed-start arm are provided with a folder containing general HIV self-management information and contact numbers for the clinic and the site coordinator. Data are collected via online forms (enrollment and medical record review), questionnaires, and SMS text messaging. Participants are consented and enrolled by study staff in person, and the baseline questionnaire is completed independently at the same visit. Remaining follow-up questionnaires at 3, 6, 9, and 12 months are prompted by an SMS text message or email and completed online. Participants and study staff are aware of study arm assignment. Delayed-start participants are given app access after completing the 6-month questionnaire. Site study staff follow the same procedure to assist with downloading the app and reviewing tutorials for participants in both the immediate- and delayed-start arms.

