### Quantitative Data Collection and Measures

Data collection is planned for a total of 18 months for each participant. Three modes of data collection are used in the study. First, site staff collect medical record data, including date of diagnosis, HIV viral load, T-cell counts, and office visit dates, for the 12 months before enrollment and for 18 months after enrollment.

Second, participants receive an email or SMS text message notification to complete follow-up electronic questionnaires at 3, 6, 9, and 12 months after enrollment. Automated reminders are sent on the scheduled completion date; if the questionnaire is not completed, additional reminders are sent 1 week and 2 weeks later. If the questionnaire coincides with an office visit or cannot be completed remotely for any other reason, study staff can administer the pending questionnaire on site using a laptop or iPad (Apple Inc). Delayed-start participants are onboarded to the app, either in person or remotely by site staff, 6 months after enrollment. This group completes baseline, 3-month, and 6-month questionnaires before downloading and initiating app use.

Third, during the intervention period, EMAs are used to collect in-the-moment information about app use (eg, “Is the Positive Peers mobile app currently downloaded to your phone?”) and related perceptions. PPA provides a natural technological interface through which such perceptions or behaviors, and their correlates within the app or the broader social environment, can be assessed in a nuanced, dynamic, and longitudinal framework.

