#### Technology Affordances

Affordances are defined as features of user-technology interactions that offer gratification of perceived needs [85,89]. These features are independent of content and reflect how a user experiences a particular type of technology. Although more or less specific typologies of media affordances have been presented [62,63,90], this study relies on a set of 10 affordances (39 items) typical of social media use and tailored to mHealth app use. These include accessibility, bandwidth, social presence, privacy, network association, personalization, persistence, editability, conversation control, and anonymity. Items were adapted to PPA use, for example, “The Positive Peers app allows me to carefully craft my message before sending it” and “The Positive Peers app makes it seem like the other person is present,” and were set on a 7-point Likert response scale.

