### Outcomes

#### Perceived HIV Stigma

The 12-item (short version) Perceived HIV Stigma Scale is used to measure overall perceived stigma and distinct dimensions (3 items each), including (1) personalized stigma, (2) disclosure concerns, (3) concerns about public attitudes, and (4) negative self-image. A 4-point Likert response format assesses each domain. Scores can be summed or averaged for each 3-item subscale and across all 12 items to yield a total stigma score, with higher scores indicating greater perceived stigma. Psychometric evaluation in a national sample of adults with HIV supported a 4-factor structure with good fit and acceptable internal consistency across subscales.

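### The Study Design section says assessments are identical in both arms to month 6, but the 39-item affordances measure and the EMAs reach only the immediate-start arm in that period

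*Protocol article*

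**What the plan says.** Study Design states that everything the two randomised arms undergo up to month 6, assessments and incentives included, is the same, and that they differ only in when they get the app. It then reads the 6-month comparison as the app's benefit over and above the effects of being in a trial.

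The schedule is set out elsewhere:

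- **Affordances timing.** Table 3 (Selection of Standardized and Validated Study Measures) collects the measure at "3 and 6 months after app initiation".
- **Affordances content.** Under Technology Affordances, "this study relies on a set of 10 affordances (39 items) typical of social media use and tailored to mHealth app use", and "Items were adapted to PPA use".
- **App start, immediate arm.** After randomisation, "site study staff assist participants randomized to the immediate-start arm in downloading the PPA from the public app store" (Enrollment, Randomization, and Data Collection Procedures).
- **App start, delayed arm.** "This group completes baseline, 3-month, and 6-month questionnaires before downloading and initiating app use" (Quantitative Data Collection and Measures).
- **Questionnaires.** Participants are prompted to "complete follow-up electronic questionnaires at 3, 6, 9, and 12 months after enrollment" (same section).
- **Self-reported outcomes.** Table 3 collects stigma, self-efficacy and social support at "Baseline, 3, 6, 9, and 12 months".
- **EMAs.** They are sent 1 and 2 months after a participant begins using the app (Ecological Momentary Assessments), and completing one gives entry to a monthly US $25 raffle (Recruitment).

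**The concern.** A delayed-start design isolates the app only if the arms are otherwise handled alike up to the comparison. Here a sizeable instrument about the app is given to one arm at exactly the two follow-up points inside the randomised period. If it shares a questionnaire with the stigma, self-efficacy and support scales, participants in that arm have a longer task for the same US $25 and may answer those scales after items about the app. Completion or responses could then differ by arm for reasons other than use of the app.

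The outcomes exposed are self-reported. Perceived stigma is a named outcome, and self-efficacy is both analysed and placed on the proposed pathway to the clinical outcomes (Planned Statistical Analysis). Separately, the protocol's own description of what the 6-month comparison estimates is inaccurate as written.

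**Working it through.** The plan gives no figure for questionnaire length, so there is none to reproduce. The check is a calendar mapping followed by a count of stated items. The sample size calculation does not enter.

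**Step 1: calendar.** Study month = month of app start + months since app start. App start is month 0 in the immediate arm and month 6 in the delayed arm.

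| Instrument | Immediate arm | Delayed arm |
|---|---|---|
| Affordances (3 and 6 months after app start) | 0+3 = 3, 0+6 = 6 | 6+3 = 9, 6+6 = 12 |
| EMAs (1 and 2 months after app start) | 1, 2 | 7, 8 |
| Stigma, self-efficacy, social support | 0, 3, 6, 9, 12 | 0, 3, 6, 9, 12 |

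Up to month 6, the affordances measure and the EMAs therefore fall in the immediate arm only. This contradicts the Study Design statement whatever the layout of the forms. The raffle attached to the EMAs means that incentives differ as well.

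**Step 2: is it the same questionnaire?** Quantitative Data Collection and Measures lists three modes: medical records, follow-up questionnaires and EMAs. The affordances items are neither record data nor among the short EMA items in Table 2. The abstract lists perceptions of digital media use as questionnaire content alongside stigma, self-efficacy and social support. The months also coincide. A shared questionnaire is the natural reading, but the article does not say so.

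**Step 3: stated items.**

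- Self-efficacy: 4 + 8 + 8 = 20 (Self-Efficacy for Managing Chronic Conditions)
- Stigma: 12 ("The 12-item (short version) Perceived HIV Stigma Scale is used to measure overall perceived stigma and distinct dimensions")
- Attitudes toward technology: 12, at month 6 but not month 3 (Attitudes Toward Technology; Table 3)
- Affordances: 39

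Month 3: shared 20 + 12 = 32; immediate arm 32 + 39 = 71; ratio 71/32 = 2.22.

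Month 6: shared 32 + 12 = 44; immediate arm 44 + 39 = 83; ratio 83/44 = 1.89.

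**Step 4: sensitivity to uncounted items.** The article gives no item count for social support or for the general self-efficacy subscale listed in Table 3. Assume S further shared items:

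| S (assumed) | Month 3, immediate vs delayed | Month 6, immediate vs delayed |
|---|---|---|
| 0 | 71 vs 32 (2.22) | 83 vs 44 (1.89) |
| 10 | 81 vs 42 (1.93) | 93 vs 54 (1.72) |
| 15 | 86 vs 47 (1.83) | 98 vs 59 (1.66) |
| 20 | 91 vs 52 (1.75) | 103 vs 64 (1.61) |

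The abstract also mentions substance use, and Planned Statistical Analysis mentions resilience, both without a count or timing. Any such shared items lower the ratios further. The absolute difference stays at 39.

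**The case against.** **Some asymmetry is unavoidable.** Items that name the app can be answered only by people who have it, and measuring process in users alone is ordinary practice. This stands. The issue is the claim of identical assessments, and whether these items touch the outcome scales.

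**The layout is inferred.** The affordances block may come last or may already be a separate REDCap form, and an article commonly leaves such detail to the full protocol. This also stands. If the block comes last, any influence on earlier answers should be small. Total burden would still differ by arm, and the Study Design text would still be wrong.

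**The main outcomes are not measured here.** The primary objective concerns engagement in care and viral suppression, both taken from records (Clinical Outcomes). A reader might infer that the primary comparison is biased by the longer form; the document does not support that.

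**A bias figure is tempting.** A 10-point response deficit in one arm, with non-responders 0.5 to 1 SD worse on stigma, would shift the respondents' arm difference by 0.10 × 0.5 = 0.05 to 0.10 × 1 = 0.10 SD in favour of the app. Neither input is in the document, and the direction follows only from assuming that non-responders are worse. The sum also describes a complete-case comparison. The plan uses maximum-likelihood mixed models under missing at random (Power Analysis), which draw on earlier responses, and it has repeated reminders and on-site completion. Those models could not remove a change in answers caused by form content, but nothing shows that such a change occurs. The affordance items cover matters such as accessibility, bandwidth and editability, and participants already know their arm.

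**Conclusion.** The contradiction is established: in the first 6 months the affordances measure and the EMAs go to the immediate arm only, while Study Design says assessments do not differ. The stated difference is 39 items at each of months 3 and 6 (71 against 32 and 83 against 44). With 10 to 20 further shared items assumed, the ratio falls to 1.75–1.93 at month 3 and 1.61–1.72 at month 6.

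That this affects the questionnaire carrying stigma, self-efficacy and social support rests on the inference that the items share a form. On that reading burden differs by arm, and context possibly does too, depending on the unstated item order. The consequence is a plausible but unquantified threat to the self-reported secondary outcomes at 6 months. It does not extend to the measurement of viral suppression or retention. The point merits correction because the remedy is nearly free and Study Design makes identical assessments a premise of its interpretation.

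**What to change.** 1. Keep the outcome questionnaire (stigma, self-efficacy, social support and, where scheduled, attitudes) identical in content and order in both arms at months 3, 6, 9 and 12.
2. Field the affordances items as a separate REDCap form that opens only after the outcome questionnaire is submitted, and count the outcome questionnaire alone as completion. If this is already the practice, say so.
3. Correct Study Design to state that the affordances measure and the EMAs, with their raffle, differ by arm in the first 6 months. Reordering the forms does not resolve that statement.
4. Recruitment opened on June 3, 2024, so if the layout changes, record which form version each participant received.

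The cost is a change to the REDCap forms and a wording change in the protocol. The small downside is that some participants may skip the separate affordances form. No measure is dropped and the sample size is unaffected.

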#### Participant Characteristics

Measured sociodemographic characteristics collected at baseline include age, ethnicity and race, biological sex, sexual orientation, sexual identity, marital status, and educational attainment. Measures were derived from the PhenX toolkit [82]. The toolkit measures are concise and widely used across health behavior studies involving marginalized groups.

#### Social Determinants of Health

The American Academy of Family Physicians developed an index of brief measures to serve as a screening tool for social determinants of health [83]. Measured social determinants of health include employment, housing, food and transportation insecurity, finances, and personal safety. The PhenX Toolkit provided measures of internet access, access to health technology, and general social media use.

#### Attitudes Toward Technology

The Media and Technology Usage and Attitudes Scale (MTUAS) [84] is a comprehensive 60-item measure designed to assess behaviors and attitudes across a wide variety of technologies and platforms. This study uses a version of the MTUAS attitudes subscale adapted to the PPA. This scale includes 12 five-point response items focused on measuring positive and negative attitudes toward technology use in general, as well as a third subscale that measures technology dependence. The subscales are reliable, and scores are significantly correlated with other measures of daily media use and technology-related anxiety.

#### Technology Affordances

Affordances are defined as features of user-technology interactions that offer gratification of perceived needs [85,89]. These features are independent of content and reflect how a user experiences a particular type of technology. Although more or less specific typologies of media affordances have been presented [62,63,90], this study relies on a set of 10 affordances (39 items) typical of social media use and tailored to mHealth app use. These include accessibility, bandwidth, social presence, privacy, network association, personalization, persistence, editability, conversation control, and anonymity. Items were adapted to PPA use, for example, “The Positive Peers app allows me to carefully craft my message before sending it” and “The Positive Peers app makes it seem like the other person is present,” and were set on a 7-point Likert response scale.

#### PPA Engagement

Following pilot study methods, intervention exposure is measured in terms of frequency of app use (number of logins and time spent) and engagement with its functions (eg, number of articles read, number of entries into a function, number of posts or replies) [17]. Participant intervention exposure is tracked natively in the PPA in real time and associated with the user’s study ID. Every screen tap for each app function is counted and aggregated in monthly reports. Community forum posts and replies are tracked verbatim, with time and date stamps. User data are separated from administrator and study staff data for evaluation using unique study IDs.

#### Self-Efficacy for Managing Chronic Conditions

Self-efficacy is measured in this study using the PROMIS instruments on self-efficacy for managing chronic conditions [91] and includes self-efficacy for managing (1) medications and treatments (4 items), (2) emotions (8 items), and (3) social interactions (8 items). Published validation efforts showed good concurrent validity and internal consistency [91]. Subscale items have 5 response options ranging from 1=I am not at all confident to 5=I am very confident.

#### Social Support

The PPA offers social support from others through the community forum and chat functions. Perceptions of social support will be tracked prospectively from baseline using the Medical Outcomes Study Social Support measure [87]. This measure is highly reliable and predictive of psychosocial outcomes across multiple chronic diseases [92,93].

This version includes 5-point Likert items that measure support across 3 dimensions: (1) emotional/informational support, (2) tangible/instrumental support, and (3) positive social interaction (ie, companionship). A fourth subscale, affectionate support, was beyond the scope of this study and was not included in the questionnaires.

### Outcomes

#### Perceived HIV Stigma

The 12-item (short version) Perceived HIV Stigma Scale is used to measure overall perceived stigma and distinct dimensions (3 items each), including (1) personalized stigma, (2) disclosure concerns, (3) concerns about public attitudes, and (4) negative self-image. A 4-point Likert response format assesses each domain. Scores can be summed or averaged for each 3-item subscale and across all 12 items to yield a total stigma score, with higher scores indicating greater perceived stigma. Psychometric evaluation in a national sample of adults with HIV supported a 4-factor structure with good fit and acceptable internal consistency across subscales.

#### Clinical Outcomes

Retention in HIV care and viral suppression are measured using standardized performance measures developed by the HRSA/HIV/AIDS Bureau [89]. Measures selected for this study are retention in HIV medical care (2 or more visits separated by at least 90 days for HIV care within the measurement year) and HIV load suppression (the most recent viral load <200 copies/mL during the measurement year). Values for outcome variables (engagement in care and viral suppression) are derived from a retrospective medical record review conducted by site study staff using a study-specific form. Engagement in care is determined by at least one office visit with an HIV clinician per 6-month interval for 12 months before and 6 months after study enrollment. Viral suppression is determined by assessing the participant’s viral load, as noted in laboratory values, typically required at least every 6 months per the standard of care. A value of <200 copies/mL is considered suppressed. Values for each variable are established for the year before study enrollment, at baseline enrollment, and then at 6-month intervals for 18 months.

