## Methods

### Study Design

Specific aims and corresponding hypotheses will be evaluated in a randomized controlled trial that compares HIV outcomes in patient groups randomized to either immediate or delayed access to the PPA. The delayed-start design is intended to ensure that both randomized study conditions receive identical study procedures, follow-up, reminders, incentives, and assessments during the first 6 months of participation. The only difference is the timing of app access. Any improvement observed in the delayed-start group during this period can therefore be attributed primarily to nonspecific effects of trial participation. The primary randomized comparison at 6 months thus estimates the incremental benefit of the app beyond these common trial effects. A greater improvement in outcomes in the immediate-start group at this point would provide evidence of a specific impact of the app.

Prospective questionnaires will be administered at baseline and at 3, 6, 9, and 12 months to provide evidence for model-specific hypotheses and the mediating effects of covariates and demographics. We have included an opportunity for patients who decline full study participation to grant permission to the PoPIT team to abstract their HIV outcomes from medical records on the same schedule as full study participants. This observation-only arm includes only the baseline questionnaire and medical record review of study outcomes. The inclusion of an observational cohort in the randomized controlled trial design strengthens external validity by enabling comparison of trial participants with the broader clinic population. By comparing outcomes from both randomized controlled trial arms with those of the observational cohort, we will gain additional insight into how trial participation may influence outcomes and how the intervention might be further adapted for a more diverse clinical population.

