### Sample Population

The study is designed to evaluate the effects of the PPA intervention among the age group most likely to be newly diagnosed with HIV in the United States: adolescents and young adults. This cohort is challenged by a propensity for greater risk behavior, lower health literacy and management skills, and typically less favorable social determinants of health. Potential participants are identified as patients at 1 of 5 HIV care organizations serving as study sites, located across 6 priority jurisdictions where HIV transmission occurs most frequently. Patients are screened to determine whether they meet all necessary inclusion criteria for study participation (Textbox 1).

Positive Peers Intervention Trial eligibility criteria.Inclusion criteriaHIV-positive status, either newly diagnosed within the last 12 months, out of care (without an office visit in the last 12 months), or not virally suppressed (viral load >200 copies/mL within the last 12 months).Adolescents and young adults aged 13-34 receiving care at one of the study sites.Identification with a sexual, gender, racial, or ethnic minority.Participant’s capacity to provide informed consent (aged >16 years) or assent to participate (aged <16 years).Ownership of a smartphone/tablet (either iOS or Android) capable of supporting the Positive Peers mobile app.Ability to read English.Exclusion criteriaPrevious use of the Positive Peers mobile app.Adults older than age 34 at the time of enrollment.Not a patient at one of the participating clinical sites.

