### Power Analysis

Group sample sizes of 106 in the Positive Peer group and 106 in the control group achieve 90% power to detect a difference between group proportions of 0.20. This is the minimum sample size required in each group to detect the desired difference in proportions. The proportion in group 1 (the treatment group) is assumed to be 0.60 under the null hypothesis and 0.80 under the alternative hypothesis. The proportion in group 2 (the control group) is 0.60. The test statistic used is the 2-sided *Z* test with pooled variance. The significance level of the test was set at .05. Several assumptions regarding baseline viral suppression were tested based on the literature. The current sample size is based on 63% viral suppression at baseline and a planned 80% in the intervention group. If baseline viral suppression is lower, a smaller sample size would be needed to demonstrate a 20% improvement in viral suppression. Based on this estimation, we aim to recruit and randomize 250 eligible individuals to the study from 6 clinic sites over 24 months, allowing for potential loss to follow-up. It is important to note that patients without documentation of a clinic visit during the assessment period are designated as out of care and will be assumed to be HIV virally unsuppressed. Available data on other outcomes and covariates, however, will be handled using mixed-effects models, which employ maximum likelihood estimation and assume missing-at-random patterns to support valid inferences.

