### Planned Statistical Analysis

Aims 1 and 2 entail data collection and analysis to provide evidence of PPA effectiveness. Outcomes include retention in HIV care (proportion of enrolled patients with laboratory results in each 6-month period of the study), HIV load suppression (proportion of enrolled patients whose viral load measurement at 6 months in the study is <200 copies/mL), as well as self-reported psychosocial variables, specifically perceived technology affordances, attitudes toward technology, and self-efficacy for managing chronic conditions. We expect that key demographics, technology covariates, and PPA use will predict self-efficacy, which will be directly associated with (1) retention in care, (2) viral suppression, and (3) HIV-related perceived stigma. Additionally, we plan to test potential covariate mediation and examine theoretical linkages in our model of PPA effects.

Analyses of repeated measures will be performed using generalized linear mixed-effects models with a logit link function for binary outcomes (ie, viral suppression and engagement in care) and linear mixed-effects models for continuous outcomes (eg, perceived stigma, resilience). Time will be treated as a fixed, repeated factor within patients, and patient-specific random effects will be included to account for within-patient correlation. To appropriately model the hierarchical structure of observations nested within patients and patients nested within sites, the site will be included as a random effect, providing an estimate of between-site variability. Multilevel mediation models will be used to evaluate potential mediating effects of covariates. *P* values will be adjusted using Bonferroni or Benjamini-Hochberg correction procedures to control the family-wise type I error rate due to multiple comparisons across distinct psychological outcomes.

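### Prior-year engagement cannot be met by patients diagnosed less than 6 months before enrollment and is zero for out-of-care entrants, so pre-to-post gains arise without any app or trial effect

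*Protocol article*

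**What the plan says.** Clinical Outcomes defines engagement as "at least one office visit with an HIV clinician per 6-month interval for 12 months before and 6 months after study enrollment". It then schedules the measurements: "Values for each variable are established for the year before study enrollment, at baseline enrollment, and then at 6-month intervals for 18 months".

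The eligibility box under Sample Population admits patients by any one of three routes: "newly diagnosed within the last 12 months, out of care (without an office visit in the last 12 months), or not virally suppressed".

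Study Design names the main inference: "The primary randomized comparison at 6 months thus estimates the incremental benefit of the app beyond these common trial effects". It also interprets change within the control arm: "Any improvement observed in the delayed-start group during this period can therefore be attributed primarily to nonspecific effects of trial participation". The same section plans to compare both randomized arms with a non-randomized observation-only cohort.

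Quantitative Data Collection and Measures says that site staff abstract date of diagnosis, viral loads and office visit dates for the 12 months before enrollment. The article does not say how the prior-year value is derived for a patient whose diagnosis falls inside that year.

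**The concern.** The look-back window for the outcome and the look-back window for eligibility are the same 12 months, and the two rules interact.

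For recently diagnosed patients, the engagement rule asks for HIV care at a time when there was no diagnosis. Someone diagnosed 2 months ago who has kept every appointment gets the same code as someone who dropped out of care. For out-of-care entrants, the value is a true record, but the entry criterion has placed it at its floor. In addition, the bar before enrollment (two intervals) is higher than the bar at 6 months (one interval).

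All three features push pre-to-post change upward. Two uses in the article are exposed. The first is the statement that delayed-start improvement mainly reflects trial participation, which does not mention selection. The second is the comparison with the observation-only cohort, because nothing balances its entry routes against those of the randomized arms.

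**Working it through.** The article gives no figure for engagement, so there is none to reproduce. Its sample size (106 per arm, 0.60 versus 0.80) concerns viral suppression and is untouched by this point.

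**Step 1. The rules set against each other.** Split the prior year into an earlier interval (12 to 6 months before enrollment) and a later one (6 to 0 months).

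| Entry route | Earlier interval | Later interval | Prior-year value |
|---|---|---|---|
| Diagnosed less than 6 months ago | HIV-care visit impossible | possible | always not engaged |
| Diagnosed 6-12 months ago | possible, in shortened time | possible | can be met |
| Out of care | no visit, by entry rule | no visit, by entry rule | always not engaged (true) |
| Not virally suppressed | unconstrained | unconstrained | can be met |

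**Step 2. Share fixed by construction among the newly diagnosed.** Assumptions, not in the documents: diagnosis dates uniform over the previous 12 months, so half fall in the last 6; newly diagnosed share of 25%, 40% or 60%.

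Share = 0.5 × newly diagnosed share: 0.5 × 0.25 = 0.125; 0.5 × 0.40 = 0.20; 0.5 × 0.60 = 0.30. Of the 250 patients to be randomized, that is about 31 (0.125 × 250) to 75 (0.30 × 250). This is an upper limit on those wrongly labelled, since some will in fact have missed visits since diagnosis. If sites enroll mostly soon after diagnosis, the factor exceeds 0.5.

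**Step 3. Apparent gain with no effect of app or trial.** Further assumptions: the same visit probability p in every open interval for every patient, independent between intervals; routes treated as exclusive, each with a share of 25-50%.

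- Pre = (newly diagnosed share × 0.5 × p²) + (out-of-care share × 0) + (unsuppressed share × p²)
- Post at 6 months = p
- Apparent gain = p − Pre

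| p | Shares (new, out of care, unsuppressed) | Pre | Post, 6 months | Gain | Gain, two intervals each side (p² − Pre) |
|---|---|---|---|---|---|
| 0.6 | 0.25, 0.25, 0.50 | 0.225 | 0.60 | 0.375 | 0.135 |
| 0.8 | one third each | 0.320 | 0.80 | 0.480 | 0.320 |
| 0.9 | 0.25, 0.50, 0.25 | 0.304 | 0.90 | 0.596 | 0.506 |

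Over p from 0.6 to 0.9 and all mixes tried, the gain runs from 0.38 to 0.60. With two intervals on each side it runs from 0.14 to 0.51.

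**Step 4. Where the gain comes from** (p = 0.8, equal thirds, total 0.48).

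- Unequal windows: p − p² = 0.80 − 0.64 = 0.16
- Diagnosed less than 6 months ago: 1/3 × 0.5 × 0.64 = 0.107
- Out-of-care entry: 1/3 × 0.64 = 0.213
- Sum: 0.16 + 0.107 + 0.213 = 0.48

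The out-of-care part assumes that these patients visit after enrollment as often as the others. If they return less often, it shrinks.

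**Step 5. The observation cohort.** At p = 0.8, a group with equal thirds shows a gain of 0.48 and a group with shares 0.25, 0.25, 0.50 shows 0.40. The difference of 0.08 comes from route mix alone.

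**The case against.** The strongest reply is that the prior-year value has no stated analytic role. Planned Statistical Analysis defines retention and suppression in study time and never names a pre-to-post contrast. Table 3 is a collection schedule. The main comparison is randomized and concurrent, which is the standard protection against drift after selecting patients at a low point. Coding of intervals before diagnosis could sit in a fuller document.

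Much of this stands, and it rules out several stronger readings that a reader might infer:

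- **That no newly diagnosed patient can meet the measure.** Those diagnosed about 6-12 months earlier can.
- **That zero is a wrong value for out-of-care entrants.** It correctly records their prior behavior. The difficulty is only that it can move in one direction.
- **That the prior-year value enters the mixed model.** The article says "Time will be treated as a fixed, repeated factor within patients" but does not say which time points are included.
- **That patients are labelled unsuppressed for time before diagnosis.** Power Analysis counts anyone with no visit on record in the period assessed as out of care and not suppressed. This follows directly on the allowance for loss to follow-up and reads most naturally as a follow-up rule.
- **That the primary comparison is biased.** Randomization distributes entry routes evenly in expectation, so the artefact is expected equally in both arms.

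The reply does not dispose of the rest. The engagement rule is stated, not omitted, and it yields a wrong value for an identifiable eligible subgroup. Study Design does interpret improvement within the delayed-start arm. For engagement, which is defined by visits over an interval, any earlier value from which to measure improvement must look back before enrollment.

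**Conclusion.** The concern holds in a limited form. The stated definition codes patients diagnosed less than 6 months before enrollment as not engaged regardless of attendance. Together with out-of-care entry and the two-against-one window, it inflates pre-to-post change in engagement in every group. The attribution of delayed-start improvement mainly to trial participation is therefore unsafe. The observation-cohort comparison can be distorted if route mix differs. The randomized 6-month contrast and the sample size are unaffected.

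The size cannot be known from the article. Under the assumptions in step 2, about 12-30% of patients have a prior-year value fixed by construction, before the out-of-care route is counted. The apparent gains in step 3 show that the artefact can be large, but they are not forecasts.

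**What to change.** 1. Using the date of diagnosis, code any pre-enrollment interval before diagnosis as not applicable, and state how the interval containing the diagnosis is scored.
2. State that the rule equating no documented visit with out of care and unsuppressed applies only to post-enrollment intervals.
3. State that the prior-year value is not a point in the repeated outcome series.
4. Adjust for entry route (newly diagnosed, out of care, in care but unsuppressed) in the models and in the comparison with the observation cohort.
5. Present any pre-to-post change by route, over windows of equal length before and after enrollment.
6. Amend the Study Design sentence so that delayed-start improvement is ascribed to selection and regression to the mean as well as to trial participation.

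The cost is wording and derivation only: diagnosis and visit dates are already abstracted, and no new data, visits or patients are needed. The drawback is that pooled pre-to-post figures will look less favorable.
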